**Research plan**

*Background*

According to the National Council on Technology Assessment (2004) the economic costs of depression are high. A calculation performed in 1997 showed that the direct and indirect costs of depression went up to 12 billion in one year. Depression is very common compared to other medical diagnoses - an estimation is that 15-17% are affected at some time during their lifetime (Ebmeier, 2006). A large number of people with depression are not detected and those detected, are often given the wrong treatment (Kessler, 2003).

Both pharmacological and psychotherapeutic treatment has been shown to have documented efficacy in treating depression (SBU, 2004). There is some evidence that psychological treatment may result in fewer relapses in depression than medical treatment after 18 months of treatment (SBU, 2004). Internet-based CBT treatment of depression has been shown efficacy in previous studies (Andersson et al., 2005; Andersson & Cuijpers, 2009; Vernmark et al., 2010).

Our research group has previously conducted a study of psychodynamic therapy delivered via the Internet, where the treatment has been shown to work for generalized anxiety disorder (GAD; Paxling et al., 2009). The study used a material that was based on a psychodynamic self-help book (Silverberg, 2005). In this study, the material will be adapted to suit the treatment of depression. Psychodynamic therapy has been shown to be effective in the treatment of depression (Driessen et al., 2010; Cuijpers et al., 2008). Based on these results, it is reasonable to assume that this approach can be adapted to be transmitted over the Internet.

The overall objective of this study is to investigate whether there are any differences in how the participants' symptoms of depression are affected, as measured by self-report measures and clinical interview, when they either undergo psychodynamic Internet treatment or participate in the control group. The control group will receive weekly support sessions during the treatment period. After the treatment period, the participants from this group will be offered he same treatment as the treatment group has received.

The development of Internet-based cognitive behavioral therapy (CBT) has come a long way in Sweden and worldwide and is used today in the treatment of depression, anxiety disorders and in somatic conditions such as pain (Andersson, 2009). In Stockholm and Östergötland, there are ongoing studies involving patients referred to Internet-based CBT. An Internet-based treatment is manualised and based on text materials in modular form and may contain related exercises. The typical way to provide Internet-based treatment in Sweden is in the form of self-help texts supplemented by therapist assistance, ie the treatment is so-called guided self-help (Andersson et al., 2008). In a guided self-help therapy participants communicate with and receive feedback from a therapist, which distinguishes it from the computerized treatment program in that is has therapist support. It has been shown in meta-analyses of Internet-based depression treatment that guided self-help have a better effect than non-guided self-help (Andersson & Cuijpers, 2009).

Several studies have been conducted comparing CBT treatments that been delivered via the Internet. One aim has been to increase the availability of psychological therapy, to improve cost-effectiveness and reach out to people who do not seek traditional therapy (Andersson & Carlbring, 2003). Promising results support the continued use and development of the method. Carlbring and Andersson (2006) point out the importance of an accurate assessment at baseline, and a continuous monitoring of patient response to treatment.

*Purpose and benefits of the study*

The primary purpose of this study is to examine whether guided psychodynamic therapy over the internet works for participants with a diagnosis of major depressive disorder and whether it provides clinically significant improvement in symptom reduction and clinically relevant improvement in quality of life compared with the control group.

Perhaps the main contribution the study could give is that it opens up for other treatment approaches. Psychodynamically inspired treatment method, presented in an understandable way, has not yet been tested for depression, and many clinicians identify themselves with a psychodynamic / psychoanalytic approach. Therefore, this study may become important. It may also be the case that psychodynamically inspired therapy is not working via internet in the treatment of depression. If this is the case, this will be important information as many psychodynamically oriented clinicians already engaged in therapy online (without research support).

*Patient Selection and Procedure*

The study will be advertised on the internet and in newspapers. After reading the information on our website, the participants notify their interest for the study. Subjects also sign a consent under the Personal Data Act (PUL) and sends it to the researchers. For screening, we intend to use the BDI-II, PHQ-9, GAD-7 and the Montgomery Asberg Depression Rating Scale - short version (MADRS-S). People who meet inclusion criteria of depression at screening via the Internet will be contacted by telephone and asked to participate in a clinically structured interview. A psychiatrist will then analyze the screening results and the results from the structured interview. This is particularly important when medical conditions occur.

Individuals included in the study will be randomized to one of two conditions, one is a psychodynamic guided self-help treatment and the other is weekly support contacts. Past experience has indicated that the participants offered an active intervention while they are on the waiting list has been estimated to maintain contact with the project. The control group will be offered the same treatment as the treatment group received, after the treatment period.

The treatment program consists of nine consecutive modules that participants work through with his/her therapist. Each module can be compared to a treatment session and will be administered at weekly intervals. Before starting treatment, all participants in both conditions need to fill out self-report measures forming baseline measurement. Each week will also require participants to fill out the BDI-II.

The first module begins with education and information about therapy and depression problems. Further therapy is then provided via the Internet to investigate the person’s self image problems and how it is maintained. The treatment is performed by a student from the last semester of training in the clinical psychologist programme, working under the guidance of an experienced psychotherapist with extensive clinical experience. Communication with clients is done via encrypted e-mail in a closed contact management system. All correspondence between the interviewer and clients will be filed in accordance with the patient act guidelines. Outcome measurements will be conducted after completion of the treatment, in addition to telephone interviews with all participants.

Overall structure for each weekly module:

1.Self-help text to be read by the participant.

2.Application of the material and application of the techniques in their own situation

3.Communication with therapist about the week's work.

4.Feedback from therapist.

*Time schedule and Evaluation*

1)       January 2011: Modules will be revised and therapists are trained.

2)       February 2011: Registration for the study. Applicants sign the consent under the Personal Data Act (PUL). Screening is completed.

3)       February 2011: The first selection. Telephone interviews will be conducted. Discussion of interviews. Randomization. Messages will be sent to the people who have been excluded or are randomized to a treatment group or control group. Baseline measurement.

4)       February-April 2011: Treatment.

5)       April 2011: End Measurements. Follow-up interviews. Data collection.

6)       May 2011: The control group will be offered treatment.

*Project team*

[name], principal investigator of the study, Professor, lic psychologist and certified psychotherapist, Department of Behavioural Sciences and Learning, IBL, LiU

[name] student, PTP-psychologist, IBL, LiU

[name], Department of Psychiatry, Linköping

[name], psychologist candidate, LiU

[name], psychologist candidate, LiU

[name], psychologist candidate, LiU

[name], psychologist candidate, LiU

[name], a psychologist candidate, LiU

[name], psychologist candidate, LiU

*References*

Andersson, G., Bergström, J., Holländare, F., Carlbring, P., Kaldo, V., & Ekselius, L.

(2005). Internet-based self-help for depression: a randomised controlled trial.

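### The schedule lists baseline self-report after participants are told their allocation, so baseline scores may be shifted by that knowledge

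*Protocol*

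**What the plan says.** The protocol's Time schedule and Evaluation is a numbered list in date order. Screening is completed in step 2. Step 3, dated February 2011, opens with selection and then reads "Telephone interviews will be conducted. Discussion of interviews. Randomization", followed by "Messages will be sent to the people who have been excluded or are randomized to a treatment group or control group. Baseline measurement". Treatment is step 4.

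Patient Selection and Procedure describes the same measurement: "Before starting treatment, all participants in both conditions need to fill out self-report measures forming baseline measurement". The start of treatment is the only time limit given there. Nothing in the protocol places baseline before randomization or before the allocation messages.

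The same section gives the arms: "one is a psychodynamic guided self-help treatment and the other is weekly support contacts". Controls are offered the treatment once the treatment period is over. Background says that the effect on depressive symptoms is judged "as measured by self-report measures and clinical interview".

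Some self-report is collected before randomization: "For screening, we intend to use the BDI-II, PHQ-9, GAD-7 and the Montgomery Asberg Depression Rating Scale - short version (MADRS-S"). The protocol treats these scores as screening and describes baseline separately.

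**The concern.** A baseline value is safe to subtract or adjust for because allocation cannot have influenced it. That protection is lost if people answer after learning their group. Here they would know whether guided treatment starts now or whether they get weekly support with treatment later, and they would then rate their own mood. Hope or disappointment could move those ratings.

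At stake is any estimate that uses baseline. A difference created by disclosure would be treated as a pre-existing difference between the arms, and removing it would bias the treatment effect. This is a matter of trial conduct: an analysis plan can choose which values to use, but it cannot restore answers that were never collected before disclosure.

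**Working it through.** The protocol states no sample size, standard deviation, effect size or power, so there is no figure to reproduce. The check is first of the sequence, then of how a shift would carry through.

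**Sequence**

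| Source | What it fixes |
|---|---|
| Schedule, step 2 | Screening completed |
| Schedule, step 3 | Interviews, discussion, randomization, allocation messages, baseline, in that listed order |
| Schedule, step 4 | Treatment |
| Patient Selection and Procedure | Baseline before treatment, in both conditions; no other limit |

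The items in step 3 before baseline make sense only in the order listed, so the natural reading is that baseline comes last. The Patient Selection text is compatible with that order but does not establish it.

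**How a shift carries through**

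Let disclosure move mean baseline by *s* points between arms and leave end scores unchanged.

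- Change-score comparison: bias = *s*
- Baseline-adjusted comparison (ANCOVA) with slope *b*: bias = *b* × *s*
- End scores only: bias from this source = 0

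With *s* assumed to be 1 to 3 BDI-II points and *b* 0.3 to 0.7:

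- Change score: 1 to 3 points
- Adjusted: 0.3 × 1 = 0.3 up to 0.7 × 3 = 2.1 points

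**Illustration of error rates**

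Every input is assumed: SD 10 at both times, baseline–end correlation 0.5 (so *b* = 0.5), 100 participants in two equal arms, *s* = 2, two-sided 5% test, normal approximation.

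- Adjusted SE = 10 × √(1 − 0.25) × 2/√100 = 1.73
- Bias = 0.5 × 2 = 1 point; 1/1.73 = 0.577 SE
- Rejection rate with no true effect: Φ(−1.96 + 0.577) + Φ(−1.96 − 0.577) = 0.083 + 0.006 = 0.089
- Power for a true 5-point difference, no shift: Φ(5/1.73 − 1.96) = 0.82
- Same, with the 1-point bias against treatment: Φ(4/1.73 − 1.96) = 0.64
- Correlation varied from 0.3 to 0.7: adjusted rejection rate about 6% to 17%
- Change score at correlation 0.5: SE = 10 × √(2 × 0.5) × 2/√100 = 2.0, bias 2 points or 1 SE; rejection rate Φ(−0.96) + Φ(−2.96) = 0.17

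**Direction**

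If disappointed controls score worse at baseline, they appear to improve more and treatment looks worse. The 8.9% then splits into about 8.3% false findings against treatment and 0.6% in its favour, the latter below the nominal 2.5%. The opposite shift reverses the split.

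**The case against.** The order is inferred. Step 3 is a string of fragments without an explicit *then*, and step 5 ends with data collection, which must overlap the items before it. That stands as a limit on certainty. Still, the list favours the later timing and nothing in the protocol points the other way.

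Pre-randomization values also exist: four symptom and anxiety scales at screening and a structured interview. If they served as baseline, the problem would largely disappear for symptoms, and the choice of covariate is commonly left to an analysis plan, which is not shown here. This reduces the harm. It does not help quality of life, which is part of the primary purpose and has no screening measure named.

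The harm further depends on an analysis that uses baseline, and the protocol commits to none. Clinical interview supplements self-report, and weekly support may soften any disappointment. If the effect of knowing one's group persisted to the end, a change score would partly cancel it. All of this is fair, and it is why no size can be claimed.

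Four stronger inferences are tempting but unsupported:

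- *The Patient Selection text proves that baseline follows disclosure.* It says who completes the forms and sets a latest time. It fits either order.
- *The primary purpose is defined as change from baseline.* Purpose and benefits of the study speaks of clinically significant improvement compared with control and does not mention baseline.
- *People without a baseline form will be excluded after randomization.* No such analysis set is stated, and the forms are required of everyone.
- *The order inflates false claims of benefit.* Under the disappointment mechanism the error runs mostly against treatment.

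**Conclusion.** The point holds as a flaw in the listed order of events. Carried out as written, the plan takes a subjective baseline after an allocation that cannot be masked has been disclosed. Any baseline-dependent analysis is then exposed to bias equal to the full shift for change scores, or slope times shift for adjusted scores. Whether a shift occurs, how large it is and which arm it favours cannot be learned from the documents. The 8.9% rejection rate and the fall in power from 82% to 64% show only what a 2-point shift would do under the assumed SD, correlation and sample size, with end scores unaffected; they do not estimate what this trial will suffer. The exposure is limited for symptoms by the screening scores, if they are used, and is open for quality of life.

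**What to change.** In step 3 of the schedule, move baseline measurement ahead of randomization, or at the least ahead of the allocation messages. In Patient Selection and Procedure, make randomization rather than the start of treatment the point that baseline must precede. If this was already the intended order, the edit simply removes the ambiguity.

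The cost is a short wait for forms before randomizing. Screening is already done over the internet, so one more set of forms for eligible people is a small burden.

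If the order cannot change, name the pre-randomization screening BDI-II, PHQ-9, GAD-7 and MADRS-S as the baseline values for symptoms. Because people enter on their screening scores, part of any within-arm change would then be regression to the mean. Randomization makes that equal in expectation across arms, so the between-arm comparison stays unbiased. Quality of life would have no such fallback unless a measure is added before randomization.
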